## **5 STUDY TREATMENT**

### **5.1 Identity**

All patients enrolled in the study will undergo bone marrow aspiration (150-200 mL) and withdrawal of 20 mL blood one to two days before CABG surgery at Assessment Ia.

As there is only autologous application of the stem cells each patient is his own donor. Herewith the inclusion and exclusion criteria of the study population and the assessments describe the selection and testing of the donors.

For all patients CD133+ cells will be selected from the bone marrow aspirate. For patients randomized to the active treatment group the cells will be suspended in physiological saline + 10% autologous serum. For the patients of the control group, the CD133+ cells will be stored at the manufacturer. See Section 5.8 for further details of bone marrow aspiration and Section 5.9 for further details of CD133+ cell and placebo preparation and treatment.

### **5.2 Administration**

Patients randomized to the active treatment group will be given 5 mL CD133+ cells, saline and serum suspension intramyocardially during CABG surgery (see Section 5.10 for further details on CABG surgery).

Patients randomized to placebo treatment will be given 5 mL saline plus serum solution intramyocardially during CABG surgery

For both treatment groups, the treatments will be administered intramyocardially in the infarction border zone (penumbra) during the cardiac surgical procedure. The procedure will be performed with extracorporeal circulatory support, aortic cross clamping and cardiac arrest induced by cardioplegia according to the center standards. The treatments will be administered before cross clamp release.

A series of fifteen individual injections (1 mL syringes, 26 Gauge needle) of 0.3 mL aliquots (in total 5 mL, including up to 0.5 mL rest in syringes) will be applied within 3 minutes in the region of interest (infarction border zone) at the end of bypass surgery (before the release of aortic cross clamp). No more than one injection per square centimeter should be injected. For documentation of injection sites see Figure 5.

## Left Ventricular Segmentation

[figure not shown]

**Figure 5: Left ventricular segmentation**

Patients will be treated after the standards of the centers, in accordance with the American Heart Association (AHA) guidelines for current standard of care.

### 5.3 Packaging, Labeling and Storage

The cell suspension or placebo product will be delivered in 1 mL opaque syringes which are packed for transport in an outer package. The syringes will be labeled in accordance with the applicable regulatory guidelines GCP-O §5 (2) 5 for labeling requirements for containers with no more than ten milliliters volume. The outer package will be labeled with the complete requirements in accordance with GCP-O §5 (2) (with name, address and telephone number of the Sponsor, name and strength of the product, with a note, that the medicinal product is intended for use in clinical trial, with precautions for the disposal of unused IMP, with trial center identification and patient identification number, and other details. As it is an autologous product and only very limited storage is allowed, additional notes will be on the outer package as: Do not irradiate! Pass on without delay! For immediate use!

See Section 5.9 for the preparation of the investigational product and placebo.

### 5.4 Blinding and Breaking the Blind

The study will be performed in a double-blind manner. The appearance of the final placebo and cellular product will be indistinguishable to the Investigators. Cell

concentrations of  $0.2$  to  $2.0 \times 10^6$  are not detectable by pure vision in the type of syringes used for application. The patients will be blinded to the treatment they receive. The surgeons and the Investigators involved in the preoperative and postoperative assessments will be blinded regarding the treatment group assignment (Team B). Only the laboratory personnel involved in the cell isolation process will not be blinded (Team A).

Team A (cell processing team) will be responsible for the preparation of the medicinal product as well as for the preparation of the placebo control and for randomization. This team will not be involved in patient recruitment/selection, clinical assessment, data collection or the treatment/sham injection. These unblinded team members should not reveal the identity of the study medication at any time.

Team B (treatment team) will be responsible for the patient recruitment/selection, clinical assessment, data collection, bone marrow harvest, and will perform the treatment/sham injection. The members of Team B will be unaware of the randomization code and blinded to the treatment.

In case of an emergency, and necessity for breaking the code, an emergency envelope will be available 24 hours a day, 7 days a week for a member of Team B. When breaking the code, a member of Team B will sign and date on the emergency envelope which has been unblinded. The treatment code for an individual patient can be revealed to a member of Team B only in case of an emergency, which requires knowledge of treatment. At the end of the trial all emergency envelopes will be returned to the Statistician and will be checked for integrity of the seal.

The study blind should not be broken except in a medical emergency (where knowledge of the study drug received would affect the treatment of the emergency) or regulatory requirement (e.g., for serious adverse events [SAEs] or death).

The investigator should promptly document and explain to the sponsor any code breaking (e.g. accidental unblinding, unblinding due to a serious adverse event) of the investigational product. If the blind is broken, the date, time and reason must be documented in the patient's CRF, and any associated AE report.

If an emergency unblinding becomes necessary, the Investigator should notify the Sponsor/Medical Monitor, if possible, prior to unblinding. The Investigator is responsible for opening the specified envelope, in the presence of a witness, both of whom must sign and date the envelope.

All envelopes, whether sealed or opened, must be returned to the Statistician, overviewed by the Sponsor at the end of the study.

The SMB will have access to the randomization code, and the code may be broken after appropriate discussion with the Sponsor.

If an Investigator, site personnel performing assessments, or patient, is unblinded, the patient must be withdrawn from the study and procedures accompanying withdrawal are to be performed. In cases where there are ethical reasons for the patient to remain in the study, the Investigator must obtain specific approval from LKP/Sponsor for the patient to continue in the study.

Serious unexpected suspected adverse reactions (SUSARs), which are subject to expedited reporting, should be unblinded before submission to the Regulatory Authorities.

The overall randomization code will be broken only for reporting purposes. This will occur once all final clinical data have been entered onto the database and all data queries have been resolved, and the assignment of patients to the analysis populations has been completed.

## **5.5 Drug Accountability**

The Investigator is responsible for maintaining accurate study drug accountability records throughout the study. The dispensing of the study treatment will be documented in the CRF “intra OP” on day 0.

The Investigator is responsible for ensuring that all unused or partially used study treatment will be disposed of according to TFG § 17 and the local regulations for biological products.

Study treatment which has not abandoned the manufacturer and that is determined not to be used for patient treatment anymore or supernumerous stem cells after manufacturing will be used for research or will be destroyed according to the patient information and the informed consent. The manufacturer will ensure, that disposal will follow TFG § 17 and his regulations for biological products.

## **5.6 Compliance**

The study treatment will be administered by the Investigator therefore patient compliance with study treatment will not be monitored.

Patients that are non-compliant with the study protocol such as non-attendance at study visits or refusal to undergo certain assessments may be candidates for patient withdrawal (see Section 4.3).

## **5.7 Concomitant Medications**

Any medication for the patients’ treatment according to the guidelines and the standards of the centers is permitted.

Any medication the patient takes other than the study drug, including herbal and other non-traditional remedies, is considered a concomitant medication. All concomitant medications are recorded in the CRF "Concomitant Medication": generic name, indication, route of administration, dose rate with unit of measurement, date started (before trial or date), date stopped (ongoing or date) and application (continuous or as necessary. Any change in the dosage or regimen of a concomitant medication is recorded in the CRF.

At Screening, patients will be asked what medications they are currently taking. Additionally any platelet aggregation inhibitors they have taken during the last 2 weeks will be documented. At each subsequent assessment, any new concomitant medication and any changes in concomitant medications will be documented.

The following medications will be of special interest:

|                       |                          |
|-----------------------|--------------------------|
| ACE-inhibitor         | ASS                      |
| Aldosteron-Antagonist | ATII Receptor Antagonist |
| Beta-blocker          | CSE-inhibitor            |
| Ca-Antagonist         | Diuretic                 |
| Digitalis             | Marcumar                 |
| Antiarrhythmic other  | Nitrate                  |

During CABG-surgery standard medication (narcotics etc.) will not be documented in the CRF. Only medication for support of cardiovascular system during OP will be documented.

Only medication for treatment of Adverse or Serious Adverse Events will be documented.

During stay in the Intensive Care Unit only maximum dosages of catecholamines and inotropics are documented and medication for treatment of Adverse or Serious Adverse Events.

## **5.8 Bone Marrow Aspiration, Blood Collection and Transport**

All patients enrolled in the trial will undergo bone marrow aspiration from the iliac crest. The procedure will be carried out under local anesthesia one to two days before surgery (Day -2 to -1). In total 150 to 200 mL bone marrow will be harvested. The procedure will be performed by an experienced hematologist or surgeon within a qualified operating room according to §20b German Medicinal Products Act. Furthermore, 20 mL of peripheral blood will be drawn for preparation of autologous serum. The bone marrow aspiration, blood collection, packaging, labeling and transport to the cell processing laboratory will follow SOP's developed and validated by Miltenyi Biotec GmbH.

## **5.9 CD133+ Cell and Placebo Preparation and Treatment**

The manufacturing process of CD133+ Cell Product and placebo will be performed in a central GMP laboratory assigned by Miltenyi Biotec. The manufacturing process and quality control is performed according to validated procedures and documented in accordance with full GMP requirements.

[figure not shown]

**Figure 6: Scheme of manufacturing process**

Patients will be randomized at the cell processing department in a 1:1 ratio to receive either cell product or placebo injection.

#### 5.9.1 *CD133+ Cell Product Release criteria*

To ensure consistent quality and individual safety of the cell product, it will only be released if the following specifications regarding the validated manufacturing process have been met:

- A. Minimum number of CD133+ cells =  $0.1 \times 10^6$  cells
- B. Maximum number of CD133+ cells =  $5 \times 10^6$  cells
- C. Minimum depletion of non-target cells = 2.5 log (> 99.6%)
- D. Minimum percentage of viable cells = 80%
- E. Manufacturing and Quality Control according to GMP

#### 5.9.2 *Final formulation of CD133+ Cell Product and Placebo*

The CD133+ cells after the CliniMACS selection process will be resuspended in 5 mL of saline supplemented with 10% autologous serum and will be drawn into 5x1 mL syringes. Placebo preparations will consist of 5 mL of saline supplemented with 10% autologous serum only and will be also drawn in 5x1 mL syringes. Each 5 syringes will be packed in an outer package by the manufacturer and has to be administered within a maximum of 72 hours after aspiration.

The chosen specification for the final formulation of the IMP has been set primarily according to the results of the former phase I and II studies of the LKP (Stamm et al.

2007: range  $1.08 \times 10^6$  to  $8.35 \times 10^7$ ) and further revised by additional comparative evaluation runs according to current GMP standards to the actual IMP formulation ( $0.1$ - $5 \times 10^6$  CD133+ cells).

#### ***5.9.3 Practices with final formulation of CD133+ Cell Product which do not fulfill the release requirements***

Final formulations which do not fulfill the release requirements will not be used in the study. The patient will be dropped out of the study and the treating physician and Statistician will be informed.

The Statistician will inform the Safety Monitoring Board, if the drop-out rate exceeds the calculated limit (see also 3.3).

In accordance with the patient's consent the cells which are not administered will either be used for research or will be destroyed.

### **5.10 Coronary Artery Bypass Graft (CABG)**

The basic surgical technique has not fundamentally changed for several decades. The chest is opened via a median sternotomy, the pericardium is opened, and the heart is exposed. Following cannulation of the ascending aorta and the right atrium, extracorporeal circulation is initiated. While the heart is still perfused and beating, the stenotic or occluded coronary arteries are exposed and prepared. Now, the aorta is clamped and a cardioplegic solution is delivered into the coronary system, arresting the heart and protecting the myocardium from ischemic injury. The coronary artery is incised and a bypass graft (i.e. saphenous vein, internal mammary artery, or others) is anastomosed to this incision. Once all bypass-to-coronary artery anastomoses have been constructed, the aortic cross clamp is released and the heart reperfused. Using a side-biting instrument, the anterior portion of the ascending aorta is partially clamped. Perforations are placed in the aortic wall, and the other end of the bypass graft is anastomosed to the aorta. Upon completion, blood flow through the bypass grafts is released and the patient is weaned from extracorporeal circulation. In a patient with impaired LV function, positive inotropic drugs may be necessary to support heart function for some time, and if this is not sufficient, intraaortic balloon counter pulsation can be used to support heart function until the myocardium has recovered.

All patients will receive the CABG operation as indicated. The decision to operate will be made in routine fashion by the referring cardiologist and the consulting surgeon. CABG surgery will be carried out on-pump and with cardioplegic arrest. All coronary arteries that should be, and can be, treated will be grafted. Upon completion of the distal anastomoses, the infarct area will be visualized and the cell suspension will be injected in the infarct border zone. From then on, the operation will be completed as per normal practice.

## 6 PARAMETERS AND METHODS OF ASSESSMENT

### 6.1 Efficacy Parameters

If not stated otherwise, all examinations have to be performed at the trial site. However, routine examinations that are executed at the trial site before informed consent was obtained should not be repeated provided the respective examination has been performed according to trial protocol. In order to avoid unnecessary inconvenience and risk for the patient, this data may also be used as historic data.

#### 6.1.1 *Left Ventricular Ejection Fraction (LVEF)*

LVEF will be measured by cardiac MRI, established as the gold standard for determination of LV function (LVEF and LV volumes). According to the schedule cardiac MRI will be performed at Assessment I, Assessment III and Assessment V.

LVEF at 6 months postoperatively (Assessment V), measured by MRI at rest is the *primary endpoint*.

*Secondary endpoints* include change in LVEF pre-operatively (Assessment I) with 6 months post-operatively (Assessment V). This will be assessed by cardiac MRI scans and echocardiography (see Section 6.1.5).

Cardiac MRI scans will be performed in accordance with the Schedule of Assessments (see Table 2). The analysis and interpretation of data from the cardiac MRI scans concerning LV function parameters will be done centrally by a reviewer blinded to the treatment the patient has received.

LVEDD, LVEDV, LVESD and LVEF will be recorded in the CRF. The main area of impaired LV infarction will also be recorded in the CRF and quality will be recorded as normal, akinetic, hypokinetic or dyskinetic.

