**Figure 3: Change in LVEF**

Change in LVEF (6 months follow up – preoperative value) in patients undergoing CABG and CD133+ cell injection (CABG & cells) compared with those undergoing CABG alone (CABG-only). The average gain in LVEF was 9.7% in CABG & cell patients, and 3.4% in CABG-only patients ( $p=0.009$ ). Box plots indicate 25th and 75th percentile (solid box), median (white bar), and minimum and maximum value of each dataset (whiskers).

As determined by SPECT imaging, myocardial perfusion in the area-of-interest at 6 months had improved in 4 control patients and in 11 patients who were treated with CABG & cell injection ( $p<0.05$  by chi-square test). Overall, improvement of perfusion was greater in the CABG & cell injection group than in the CABG only group (median [25th-75th percentile] = 0.95 [0.91-1.03] for CABG only patients vs. 1.02 [0.95-1.1] for CABG & cell injection patients). Figure 4 depicts representative perfusion scans from a patient who received  $5 \times 10^6$  CD133+ selected cells in the border zone of a posterior transmural myocardial infarction, where no bypass graft could be placed. It is evident that at the time of discharge there was no relevant improvement, but perfusion of the ischemic tissue had virtually normalized 4 months later. This secondary gain in tissue blood supply might be attributed to the cell injection.

[figure not shown]

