### **3.2 Endpoints**

#### Primary endpoint

The primary endpoint is LVEF at 6 months postoperatively, measured by MRI at rest. Cardiac MRI is established as the gold standard for determination of LV function (LVEF and LV volumes).

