### 4.3 Patient Withdrawal and Replacement

Patients may withdraw from the study at any time without penalty and for any reason without prejudice to his or her future medical care. All patients will be closely monitored by their individual cardiologist and general practitioner and treated as appropriate, according to the guidelines issued by the national and international cardiology organizations that relate to patients with coronary artery disease and patients with congestive heart failure. The Investigators reserve the right to conduct additional follow-up examinations.

Patients must be withdrawn under the following circumstances:

- The patient withdraws consent;
- Pregnancy. If patients are to withdraw due to pregnancy, they should be followed-up until the outcome for the mother and fetus are known.
- If serious clinical events (e.g., emergency surgery, myocardial infarction, stroke, fever  $\geq 38.5^{\circ}\text{C}$ ) occur between recruitment and planned surgery.

Patients may be required to withdraw after discussion with the Sponsor and/or Investigator for the following reasons:

- Adverse event(s);
- At the discretion of the Investigator;
- Violation of eligibility criteria;
- Deviation from the treatment plan specified in the protocol (e.g., incorrect administration of the study drug, failure to attend study visits).

In all cases, the reason(s) for withdrawal, and the primary reason, will be recorded on the case report form (CRF). If a patient is prematurely withdrawn from the study for any reason, the Investigator will make every effort to perform the evaluations described for the Early Termination Visit (see Section 7.2.6.2).

An excessive withdrawal of patients can render the study uninterpretable. Therefore unnecessary withdrawal of patients should be avoided. In case of withdrawal, all efforts should be made to complete and report the observation and justification of withdrawal in as much detail as possible. Withdrawn patients that dropped-out of the study because of SAE will not be replaced. However, patients who are not able to reach the primary endpoint because of their body size/weight may be replaced.

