**Table 2: Schedule of Assessments**

| Assessments                                    | I               | Ia                         | II             | IIa             | III                                | IV                                  | V                            | VI                                  |
|------------------------------------------------|-----------------|----------------------------|----------------|-----------------|------------------------------------|-------------------------------------|------------------------------|-------------------------------------|
|                                                | Screening       | BM transfer/
Cell Prep. | Intra-OP       | Post OP
/ICU | Hospital
Discharge e | 3-Month
FU e          | 6-Month FU/
Early termin. | 24-Month
FU                      |
| Timepoint                                      | Day -7
to -1 | Day -2 to 0                | Day 0          | Day 1           | Within 72 hrs
of discharge      | Month 3 e
(± 2 weeks) | Month 6
(±2 weeks)        | Month 24 d
(±2 weeks) |
| Informed consent                               | X               |                            |                |                 |                                    |                                     |                              |                                     |
| Patient Demographics                           | X               |                            |                |                 |                                    |                                     |                              |                                     |
| Inclusion/exclusion criteria                   | X               |                            |                |                 |                                    |                                     |                              |                                     |
| Medical history: general/cardiac /risk factors | X               |                            |                |                 |                                    |                                     |                              |                                     |

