#### 7.2.6.2 *6-Month Follow-Up post OP ( $\pm 2$ weeks, Assessment V)/Early Termination*

- Study termination
  - has the study been terminated according to protocol? If yes, proceed with Physical examination/vital signs
  - If study was early terminated:
    - Date of withdrawal/early termination
    - Reason for withdrawal/early termination (AE, at the discretion of the investigator, violation of eligibility criteria, deviation from the treatment plan specified in the protocol, pregnancy, patient withdraws consent, death, other (describe))
- Date of patient contact
- Vital signs (see Section 6.3.2.2)
- General physical examination (see Section 6.3.2.3)
- Blood sampling for laboratory tests (Hematology, Clinical Chemistry and Electrolytes; see Section 6.3.2.1)
- Blood sampling for NT-proBNP (pg/mL; to be sent to Core Lab; see Section 6.3.2.1)
- Cardiac MRI scan and echocardiography to be sent to Core Lab (see Sections 6.1.1 & 6.1.2, 6.1.5 & 6.1.6)
- Classification of heart failure with NYHA and angina with CCS (see Section 6.1.3)
- Holter and LOWN classification (historic data may be used, see Section 6.3.2.4)
- 12-lead ECG (see Section 6.3.2.5)
- Determination of MACE (see Section 6.3.1.6)
- Completion of QoL questionnaires (MLHF and SF-36; see Section 6.2.)
- 6-Minute Walk Test (6MWT, see Section 6.1.7)
- Documentation of any change in concomitant medication
- Documentation of any AE/SAE since last assessment

*7.2.6.3 24-Month Follow-Up post OP ( $\pm$  2 weeks, Assessment VI after data closure for safety reason)*

- Date of patient contact
- Vital signs (see Section 6.3.2.2)
- General physical examination (see Section 6.3.2.3)
- Echocardiography from practice based cardiologist (see Sections 6.1.1, 6.1.2, & 6.1.6)
- Holter from practicing cardiologist and LOWN classification (see Section 6.3.2.4)
- Blood sampling for laboratory tests (Hematology, Clinical Chemistry and Electrolytes; see Section 6.3.2.1)
- Blood sampling for NT-proBNP (pg/mL; to be sent to Core Lab; see Section 6.3.2.1)
- Completion of QoL questionnaires (MLHF and SF-36; see Section 6.2.)
- Performance of 12-lead ECG (see Section 6.3.2.5)
- Determination of MACE (see Section 6.3.1.6)
- Documentation of concomitant medication related to treatment of AE/SAE

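### Treated patients who leave early are scanned at exit and no month-6 MRI is planned for them, because Assessment V doubles as the early-termination visit

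*Protocol*

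**What the plan says.** - **Endpoint.** Section 3.2 defines it by time: "The primary endpoint is LVEF at 6 months postoperatively, measured by MRI at rest". Section 6.1.1 adds the visit: "LVEF at 6 months postoperatively (Assessment V), measured by MRI at rest".
- **Visit.** The Table 2 column for Assessment V is headed "6-Month FU/ Early termin" and has one timepoint, "Month 6 (±2 weeks". The heading of Section 7.2.6.2 also joins the two uses ("weeks, Assessment V)/Early Termination"). One procedure list follows, with cardiac MRI sent to the core laboratory. Its first item is a branch: "has the study been terminated according to protocol? If yes, proceed with Physical examination/vital signs"; if not, the date and reason of early termination are entered. Section 7.2.6.1 refers to the same combined form.
- **Withdrawal.** For premature withdrawal for any reason, Section 4.3 says that "the Investigator will make every effort to perform the evaluations described for the Early Termination Visit (see Section 7.2.6.2". Beyond this it only reserves the investigators' right to further follow-up examinations. Withdrawal may follow adverse events, investigator discretion, eligibility violations or treatment deviations. Section 5.4 adds withdrawal after unblinding, unless continuation is specifically approved.
- **Exception.** Patients with a cell yield below 0.5 × 10⁶ but at least 0.1 × 10⁶ count as drop-outs but stay in follow-up (Sections 3.3 and 8.1.2).
- **Analysis.** The primary set is the FAS on the intent-to-treat principle, irrespective of withdrawal (Section 8.1.3). Missing values are not replaced (Section 8.2).

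**The concern.** The analysis set and the visit plan do not fit together. An intent-to-treat comparison of month-6 LVEF needs month-6 LVEF from people who have left the trial. The protocol asks for their MRI on the way out and schedules nothing later. With no replacement of missing values, such a patient is in the FAS by name but adds no outcome to the ANCOVA.

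Much of this loss is avoidable. The study treatment is given once, during surgery, so leaving later does not change exposure, and month-6 LVEF remains well defined for any survivor. Several grounds for withdrawal are decisions of the investigator or sponsor, or follow from unblinding, so the patient may still be willing to be scanned. If the reasons for leaving differ between arms, the patients who remain are no longer a randomized comparison.

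A second, smaller matter is that the exit scan carries the same visit label that Section 6.1.1 uses to identify the primary endpoint. The label therefore does not separate the two kinds of scan.

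**Working it through.** **1. What happens to a treated patient withdrawn at, say, week 3**

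| Step | Source | Result |
|---|---|---|
| Perform the early-termination evaluations | 4.3 | MRI at about week 3 |
| Record them | 7.2.6.2, Table 2 | Entered under Assessment V |
| Month-6 MRI | no provision unless low cell count | Not scheduled |
| Primary analysis set | 8.1.3 | Patient included |
| Missing LVEF | 8.2 | Not replaced |

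If the scan is excluded because of its date, the patient has no primary outcome. If it is accepted because of its label, the value is not a 6-month value. Neither route yields the month-6 measurement.

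**2. Reproducing the planned sample size**

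Inputs (Section 8.7 and synopsis): difference 4.5, SD 7.5, two-sided α 0.05, power 90%, 15% drop-out, 1:1 allocation.

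Method: two-sample t test with non-central t and non-centrality (4.5/7.5) × √(n/2).
- n = 60: 0.6 × √30 = 3.29, power 90.3%. With n = 59, power is 89.8%. So 60 per arm is confirmed.
- Drop-out: 60/0.85 = 70.6, rounded up to 71 per arm and 142 in total. Confirmed.

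The plan therefore counts the 11 per arm lost (71 − 60) as not evaluable.

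**3. What recovering month-6 scans could give**

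Same formula:

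| Evaluable per arm | Recovered out of 11 | Power |
|---|---|---|
| 60 | 0 | 90.3% |
| 64 | 4 | 92.0% |
| 67 | 7 | 93.2% |
| 71 | 11 | 94.4% |

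For 71: 0.6 × √35.5 = 3.57. This row is a ceiling. Deaths, refusals, patients withdrawn before treatment and patients who cannot be scanned because of body size will not be recovered. The figures use the t-test setting of Section 8.7 and ignore the ANCOVA and the interim analysis.

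**4. If exit scans were counted as 6-month values (illustration only)**

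Assume that 15% of each arm has an exit scan carrying a fraction f of the 4.5-point effect, with n = 71. The expected difference is 4.5 × (1 − 0.15 × (1 − f)).

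| f | Difference | Power |
|---|---|---|
| 0 | 3.83 | 85.5% |
| 0.5 | 4.16 | 90.7% |
| 1 | 4.50 | 94.4% |

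The comparator, leaving those patients out, is 90.3%. Counting exit scans can thus lower or raise power, depending on f. The protocol gives neither f nor the share of drop-outs who would have an exit MRI.

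**The case against.** The strongest reply is that the endpoint is defined by time and the visit number in Section 6.1.1 is only a pointer. Much supports this. Assessment V has a ±2-week window. The MRI form records the scan date (Section 6.1.5), and the visit form records the date of early termination. Patients lacking a 6-month LVEF are a named reason for exclusion from the PPS (Section 8.1.2). The sample size treats drop-outs as not evaluable. Handling of off-window scans is commonly settled in the SAP, which is not shown, and a shared final and early-termination procedure list is a usual layout.

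All of that stands. A reader might infer that an MRI at withdrawal is analysed as the 6-month LVEF. The protocol does not say so, and most of its text points the other way. The supportable statement is only that the label does not itself exclude such a scan.

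A reader might also infer that exit scans carry no treatment effect, because Section 1.1.2.5 says that "at the time of discharge there was no relevant improvement, but perfusion of the ischemic tissue had virtually normalized 4 months later". That sentence concerns SPECT perfusion in one patient. For LVEF, the same section reports a significant rise already at discharge in the 15-patient safety trial. That series is uncontrolled, so it gives no between-arm effect at discharge either. Zero early effect is a bounding case, not something the protocol establishes.

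Nor is the exit scan wasted, since MRI also serves the check for unwanted tissue changes (Section 6.3.2.9).

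What the reply does not meet is the missing scan. An SAP can set a window by scan date, but it cannot recover a month-6 MRI that was never scheduled.

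**Conclusion.** The point holds in limited form. Followed as written, the protocol gives up month-6 LVEF for treated patients who leave early and could still be scanned, while its primary analysis claims to include them. The low-cell-count group shows that the protocol already accepts follow-up after drop-out; it does not extend it to other treated patients.

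The only size that follows from the planning values is the power range: 90.3% with 60 evaluable per arm, and at most 94.4% with all 71. The planned 142 patients need not change. The larger reason to act is selective loss in the primary comparison. Its size and direction cannot be determined, because the protocol does not say how many would leave early in each arm, why, or with what LVEF. A claim of a definite dilution, or of bias towards one arm, would go beyond the document.

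This is a cheap improvement that should be made. The labelling and scan-date wording would be no more than a clarification on its own.

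**What to change.** 1. **Sections 4.3 and 7.2.6.2:** extend the follow-up already used for low-cell-count patients. Every treated patient who leaves early and still consents is asked to return for MRI and echocardiography at month 6 (±2 weeks).
2. **Table 2, Section 7.2.6.2 and the CRF:** give early termination its own visit label, separate from the 6-month visit.
3. **Synopsis, Sections 3.2 and 6.1.1:** state that the primary value comes only from a core-laboratory MRI dated within the month-6 window. Exit scans stay in the database under their actual date and are not used as 6-month LVEF.

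**Cost:** protocol wording and a CRF visit split, plus one additional MRI for the patients who are also scanned at exit. Some patients will decline, and their month-6 values will remain missing.
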